### Intervention and Study Visits

#### Baseline Hospital Ward Visit

Baseline assessments are conducted in the hospital ward. Demographic information, medical history, health history (eg, long-term alcohol use and smoking status), hearing and vision measurement, baseline laboratory tests, and electrocardiography are collected from the electronic medical record. One day before surgery, patients undergo assessments, including pain measured by a visual analog scale,^28,29^ depression by the 9-item Patient Health Questionnaire,^30^ anxiety by the 7-item Generalized Anxiety Disorder Scale,^31^ insomnia by Insomnia Severity Index,^32^ and cognitive function by the Montreal Cognitive Assessment,^33^ with the aim of identifying risk factors of emergence delirium. All planned study visits are presented in the Table.

**Table. zoi200508t1:** The Schedule of Planned Investigation

Study component	Visit 1	Visit 2	Visit 3	Visit 4	Visit 5	Visit 6	Visit 7	Visit 8
Time	1 d before surgery	Before anesthesia	During anesthesia	PACU	POD 1	POD 2	POD 3	Hospital discharge
Eligibility screen	X	−	−	−	−	−	−	−
Informed consent	X	−	−	−	−	−	−	−
Demographic characteristics	X	−	−	−	−	−	−	−
Randomization	X	−	−	−	−	−	−	−
Intervention	−	X	−	−	−	−	−	−
MoCA	X	−	−	−	−	−	−	−
VAS	X	−	−	X	X	X	X	−
PHQ-9	X	−	−	−	−	−	X	−
GAD-7	X	−	−	−	−	−	X	−
ISI	X	−	−	−	−	−	X	−
EEG frequency spectrum	−	X	X	X	−	−	−	−
Blood draw for biomarkers	−	X	−	X	−	−	−	−
CAM-ICU	−	−	−	X	X	X	X	−
Nausea and vomiting	−	−	−	X	X	X	X	−
Adverse events	−	−	−	X	X	X	X	−
Hospital stay	−	−	−	−	−	−	−	X

Abbreviations: CAM-ICU, Confusion Assessment Method for the Intensive Care Unit; EEG, electroencephalography; GAD-7, 7-item Generalized Anxiety Disorder Scale; ISI, Insomnia Severity Index; MoCA, the Montreal Cognitive Assessment; PHQ-9, 9-item Patient Health Questionnaire; POD, postoperative day; VAS, visual analog scale; X, present; minus sign, absent.

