### Outcomes

The primary outcome in this study is the incidence of emergence delirium within 1 hour after tracheal extubation measured using the validated Chinese version of the CAM-ICU.^36^ The CAM-ICU was validated against the *Diagnostic and Statistical Manual of Mental Disorders* (Fifth Edition) criteria for delirium in PACU settings based on the guideline.^38^ With a specificity of 98% and low sensitivity, we may detect the positive delirium cases conservatively in this study.^39^ The positive CAM-ICU test result requires the presence of (1) acute changes in mental status with a fluctuating course and (2) inattention, with either (3) disorganized thinking or (4) altered level of consciousness. Patients with delirium may display hyperactive or hypoactive signs. Hyperactive delirium is defined as RASS scores from 1 to 4, and hypoactive delirium is defined as RASS scores from −3 to 0.^40^ Secondary outcomes include (1) incidence of postoperative delirium within 3 days after surgery (defined as positive CAM-ICU test result); (2) nausea and vomiting within 3 days after surgery; (3) postoperative pain intensity at PACU discharge and 24, 48, and 72 hours after surgery, measured using the visual analog scale (scores range from 0-10, with higher scores indicating greater pain); (4) adverse events (cardiac arrhythmias, cardiogenic shock, and other unexpected adverse events) within 3 days after surgery; (5) length of hospital stay; and (6) all-cause mortality during hospitalization.

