### Secondary Outcome Analysis

For secondary outcome analyses, the Mann-Whitney test will be used for length of hospital stay, whereas the χ^2^ test or the Fisher exact test will be used for categorical variables, including incidence of postoperative delirium within 3 days after surgery, nausea and vomiting, postoperative pain, and adverse events. For analysis of all-cause mortality during hospitalization, we will use Kaplan-Meier curves, with a log-rank test for between-group comparison. The Cox proportional hazards model will be used to estimate the hazard ratio among patients in the tropisetron group compared with the placebo group with adjusting for potential confounding factors.^42,43^

All statistical tests will be 2 sided, and statistical significance will be defined as *P* < .05. Statistical analysis will be performed with SPSS software, version 22.0 (SPSS, Inc).

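### In-hospital mortality is to be analysed by Kaplan-Meier, log-rank and adjusted Cox without saying how patients discharged alive are handled; a comparison of proportions would fit the outcome better

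*Protocol article*

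**What the plan says.** Four statements in the Protocol article bear on this point.

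- **Outcome.** The section Outcomes lists, as the sixth and last secondary outcome, "all-cause mortality during hospitalization". No day is given at which status is read.
- **End of follow-up.** In the schedule table under Baseline Hospital Ward Visit, the last column (Visit 8) is "Hospital discharge". Nothing is scheduled later.
- **Analysis.** Secondary Outcome Analysis states: "For analysis of all-cause mortality during hospitalization, we will use Kaplan-Meier curves, with a log-rank test for between-group comparison". It adds: "The Cox proportional hazards model will be used to estimate the hazard ratio among patients in the tropisetron group compared with the placebo group". Covariate adjustment of this model is announced, but the factors are neither named nor counted.
- **Length of stay.** This is a secondary outcome in its own right. The same section says that "the Mann-Whitney test will be used for length of hospital stay".

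The article gives no censoring rule for patients who go home alive, no expected mortality, no expected number of deaths and no expected length of stay. The sample size rests on the primary outcome alone.

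**The concern.** A patient who has gone home can no longer die in hospital. Live discharge is therefore a competing event for this outcome. Censoring is harmless to a Kaplan-Meier curve only if those censored carry the same later risk as those still observed. Here patients leave because they have recovered, and the event as defined can no longer happen to them. A curve that censors them estimates what would occur if everyone stayed in hospital indefinitely, which is not the outcome listed.

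The comparison between arms is exposed in a different way. The hazard of death per day in hospital depends on how many days are spent there. The Introduction links delirium with longer stay, and stay is itself compared between arms, so the trial allows for the drug changing it. If it does, the hazard ratio and the in-hospital risk ratio part company.

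At stake is a safety-relevant result: a curve showing several times the true risk, or a hazard ratio that reflects earlier discharge and not more deaths. Separately, elective patients of ASA class I to III may have too few deaths for a multivariable model.

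**Working it through.** **Plan's own figure.** There is none for mortality to reproduce. The only related number is the sample size: 640 / (1 − 0.15) = 752.9, so 753 per arm against the 754 stated. The difference is immaterial here; the total is 1508.

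**Inputs.** From the Protocol article: 1508 patients randomised 1:1, follow-up for death to discharge, Kaplan-Meier, log-rank and Cox. Assumed, because the article is silent: in-hospital mortality of 0.25% to 1%, mean stay of 5 to 10 days, constant daily hazards of death (h) and of live discharge (g), and censoring at live discharge.

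**Step 1: level of the curve.** The true in-hospital risk is h / (h + g), and the mean stay is 1 / (h + g). With discharge censored, one minus Kaplan-Meier at day t is 1 − exp(−h·t).

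For 1% mortality and a 7-day mean stay, h = 0.01 / 7 = 0.00143 per day:

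- day 14: 1 − exp(−0.0200) = 2.0%
- day 30: 1 − exp(−0.0429) = 4.2%

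Day-30 readings over the assumed range:

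| Mean stay | True risk | 1 − KM at day 30 |
|---|---|---|
| 7 days | 0.25% | 1.1% |
| 7 days | 0.5% | 2.1% |
| 7 days | 1% | 4.2% |
| 5 days | 1% | 5.8% |
| 10 days | 1% | 3.0% |

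The overstatement does not require any difference between arms. A crude proportion, or a cumulative incidence curve once all patients have left, returns the true risk in every row.

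**Step 2: the comparison.** Let the treated arm be discharged at k times the control rate.

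- *Equal 1% risk in both arms.* The treated death hazard must be (0.01 / 0.99)·g·k, and the control hazard is (0.01 / 0.99)·g. The hazard ratio is therefore k: 1.10, 1.25 and 1.50 for discharge 10%, 25% and 50% faster, although the risks are identical.
- *Equal death hazards (hazard ratio 1).* The risk ratio is [0.01 / (0.01 + 0.99k)] / 0.01, that is 0.91, 0.80 and 0.67 for the same values of k.
- *Equal discharge rates (k = 1).* Both ratios are 1 and nothing is distorted.

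**Step 3: number of deaths.** Expected deaths are 1508 × mortality:

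- 0.25%: 3.8
- 0.5%: 7.5
- 1%: 15.1

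Under the common guide of 10 deaths per model parameter, treatment plus one covariate needs 20 deaths (20 / 1508 = 1.3% mortality). Treatment plus three needs 40 (2.7%), and treatment plus five needs 60 (4.0%). Over the assumed range, even one covariate exceeds what the guide allows.

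**The case against.** The strongest reply is that the article never says discharged patients are censored. They might be carried as alive to a common day, in which case the curve would equal the crude proportion and most of the problem would vanish. Censoring rules and covariate lists are also often left to a fuller document, and the article points to a full protocol in a supplement that is not shown. This stands in part. Censoring at discharge is an inference from an outcome that ends at discharge, a schedule that ends there, and the ordinary use of the named methods. The point must be put conditionally.

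Second, the log-rank test and Cox model remain valid for the cause-specific hazard of death, and they mislead about in-hospital risk only if stay differs by arm. This stands. The article gives no expected stay and no expected effect on it, so the ratios of 1.10 to 1.50 illustrate a mechanism and do not forecast a result.

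Third, the day-30 readings lie in the tail. Under the assumed 7-day exponential stay, exp(−30 / 7) = 1.4% of patients remain, about 10 per arm of 754. Nothing says that a day-30 value will be reported. That is fair, but at day 14, when exp(−14 / 7) = 13.5% remain, the curve already reads double.

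Fourth, imprecision from few deaths is not a fault of the Cox model. With 8 deaths the standard error of the log hazard ratio is 2 / √8 = 0.71, a confidence interval spanning a factor of about 4 either side. Fisher's exact test would be about as imprecise on the same deaths. This stands: the case against the adjusted model rests on deaths per parameter, not on the width of that interval.

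**Conclusion.** The concern holds in conditional form. The article fixes time-to-event methods for an outcome that ends at discharge and leaves open how live discharges are treated. If they are censored, the curve overstates in-hospital death risk, by roughly two times at day 14 and four times at day 30 under a 7-day exponential stay with constant hazards. The hazard ratio then answers a different question from the outcome listed whenever stay differs between arms.

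A reader might infer more: that the plan does censor at discharge, that the treatment comparison is therefore biased, and that the adjusted model cannot be fitted. The documents do not support these. No censoring rule is written, the comparison is undistorted if stay is equal, and neither a mortality rate nor a number of covariates is given. What can be said is that, at an assumed 0.25% to 1% mortality, about 4 to 15 deaths are unlikely to support covariate adjustment.

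Mortality is the last-listed secondary outcome and plays no part in the sample size or the primary analysis. The trial's main conclusion is untouched. The change is still worth making, because mortality carries safety weight and the better analysis is also the simpler one.

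**What to change.** In Secondary Outcome Analysis, replace the mortality sentences with the following:

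- Report in-hospital deaths as number and percentage per arm, compared by Fisher's exact test, with a 95% CI for the risk difference (exact or Newcombe).
- Drop the adjusted Cox model. Randomisation leaves little need for confounder adjustment here.
- If a curve over time is wanted, plot cumulative incidence of in-hospital death by arm, with discharge alive as the competing event.

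Fisher's test is already named in that section for categorical outcomes, and the data are already collected. The cost is a change of wording, with no new visits, patients or measurements. What is lost is a time-to-event hazard ratio for mortality.

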### Study Design and Setting

The study is being conducted in Beijing Chaoyang hospital affiliated with Capital Medical University, Beijing, China. The trial has been approved by the Medical Ethics Committee of the Chaoyang Hospital, Beijing. This study protocol is strictly in accordance with the Standard Protocol Items: Recommendations for Interventional Trials (SPIRIT) reporting guideline.^26,27^

The study is a double-blinded, randomized placebo-controlled trial that includes 1508 patients undergoing noncardiac surgery. Potential participants undergoing noncardiac surgery will be screened for eligibility criteria. All enrolled patients will be randomly divided into either the tropisetron group or placebo group at a 1:1 ratio. The primary end point is the incidence of emergence delirium.

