### Sample Size Calculation

The sample size calculation is based on the primary outcome. According to previous studies, the incidence of delirium diagnosed in the PACU ranged from 3.7% to 22.2%.^7,8,9^ We assumed an emergence delirium incidence of 15% in the control group and a 6% reduction (the clinical limit of superiority) in the intervention group. With a power of 80% and 1-sided α = .05 and using superiority tests for 2 proportions, 640 patients per group are required. With a dropout rate of 15%, the final planned total sample size is 754 randomized patients in each group. The sample size calculation was performed on PASS software, version 14.0 (Number Cruncher Statistical Software).

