### Primary Outcome Analysis

The primary outcome of our analysis is the incidence of emergence delirium. Comparisons in delirium incidence between the 2 groups will be assessed with a χ^2^ test, and 95% CIs will be calculated for the difference in delirium incidence.

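### The sample size and its 80% power are stated for a 1-sided .05 test, but the primary outcome will be tested 2-sided at .05, so the stated α and power do not describe the planned test

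*Protocol article*

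**What the plan says.** Two parts of the protocol article set an error rate for the same outcome.

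- **Sample Size Calculation.** The calculation is for the primary outcome, emergence delirium. The section states: "We assumed an emergence delirium incidence of 15% in the control group", and "a 6% reduction (the clinical limit of superiority) in the intervention group". It continues: "With a power of 80% and 1-sided α = .05 and using superiority tests for 2 proportions, 640 patients per group are required". After an allowance of 15% for dropout, the plan is 754 randomized per group, 1508 in all.
- **Primary Outcome Analysis and Secondary Outcome Analysis.** The groups are compared with a χ² test, and "95% CIs will be calculated for the difference in delirium incidence". The last paragraph under Secondary Outcome Analysis then says "All statistical tests will be 2 sided", with significance at P < .05. Although it stands under the secondary heading, it speaks of all tests, and the primary outcome section gives no other α.

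Nothing in the article explains why the design uses one sidedness and the analysis the other.

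**The concern.** A 1-sided test at .05 accepts a 5% chance of wrongly declaring benefit. A 2-sided test at .05 accepts 2.5% in that direction. The 95% interval goes with the second; a 1-sided .05 test would go with a 90% two-sided interval. The power in the sample size paragraph was thus computed for a test the investigators do not plan to run.

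Two things are at stake. First, a reader cannot take the 80% as the power of the planned analysis. Second, a primary result falling between the two thresholds would meet the criterion used in the sizing and fail the one in the analysis plan. That is an awkward discrepancy to leave in print while the trial is recruiting.

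**Working it through.** **Inputs.** Control rate 15%, reduction 6 points (read as 15% versus 9%), power 80%, 1-sided α = .05 and 640 per group, all from Sample Size Calculation; 1:1 allocation from Study Design and Setting; 2-sided .05 from the end of Secondary Outcome Analysis. Normal quantiles: 1.645 (1-sided .05), 1.960 (2-sided .05), 0.842 (80% power).

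**1. Trying to reproduce 640.** With unpooled variance, n per group = V × (z_α + 0.842)² / 0.06², where V = 0.15×0.85 + 0.09×0.91 = 0.2094.

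| Test, 15% vs 9%, no margin | Unpooled | Pooled | Continuity-corrected |
|---|---|---|---|
| 1-sided .05 | 360 | 362 | 395 |
| 2-sided .05 | 457 | 460 | 493 |

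The change of sidedness costs 456.5 / 359.6 = 1.27, or 27% more patients, but 640 exceeds every entry. Reading the 6% as relative (15% versus 14.1%) gives 18,979 per group 1-sided, so that does not explain 640 either. The dropout step is sound: 640 / 0.85 = 752.9, so 753 against the stated 754.

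**2. Power of 640 per group for 15% versus 9%, null of no difference.** Standard error under the null: √(2×0.12×0.88/640) = 0.01817. Under the alternative: √(0.2094/640) = 0.01809.

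- 1-sided: Φ[(0.06 − 1.645×0.01817)/0.01809] = 95.2%.
- 2-sided: Φ[(0.06 − 1.960×0.01817)/0.01809] = 91.1%.

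**3. Success thresholds at 640 per group with 15% observed on placebo.** Solve d = z × √(2p̄(1−p̄)/640) with p̄ = 0.15 − d/2.

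- z = 1.645: d ≈ 3.1 points.
- z = 1.960: d ≈ 3.7 points.

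Example between the two: 96/640 on placebo (15.0%) and 74/640 on tropisetron (11.6%), a difference of 3.4 points. The pooled rate is 170/1280 = 13.3%, the standard error 0.01897 and z = 0.03437/0.01897 = 1.81. This gives 1-sided P = .035 and 2-sided P = .070.

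**4. If 640 rests on a superiority margin (assumption).** The wording of the effect could mean that a margin was entered. A margin of 1.5 points, which the article does not state, leaves 0.06 − 0.015 = 0.045:

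- 1-sided: 0.2094 × (1.645 + 0.842)² / 0.045² = 639.3, rounded up to 640.
- 2-sided, same margin: 811.6, so 812 per group (956 after dropout). Power at 640 = Φ(0.045/0.01809 − 1.960) = 70.1%, against 80.0% 1-sided.

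This is the power of a test against a 1.5-point margin. The planned χ² test has no margin.

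**The case against.** The strongest reply is that the sidedness is not open. Sample Size Calculation lists design inputs; the decision rule is in the analysis sections, which give one answer without exception: 2-sided, P < .05. The mismatch also runs in the safe direction, since 2.5% rather than 5% is allowed for a false claim of benefit. And 640 per group is more than either sidedness needs for 15% versus 9%.

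All of this stands, and it rules out three stronger readings that a reader might infer:

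- **That the sidedness can be chosen after the data are seen, doubling the false-positive risk.** This would require setting aside the explicit 2-sided statement. If that statement is followed, type I error is not inflated.
- **That the trial is underpowered.** On the stated rates and the planned χ² test, power is about 91%. The 27% is the general price of changing sidedness, not a deficit here.
- **That power drops from 80% to 70%.** This holds only for a margin-based test with a 1.5-point margin, a value found by working back from 640. The article neither states that margin nor plans such an analysis.

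The reply does not remove the mismatch itself. The article prints an α and a power that are not those of its planned primary test.

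**Conclusion.** The inconsistency is real and limited in effect. The stated 1-sided α = .05 and 80% power do not belong to the planned 2-sided test. The two rules differ by about 0.6 points in the observed reduction needed (3.1 versus 3.7, assuming 640 evaluable per arm and 15% observed on placebo), and the planned rule is the stricter.

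With 15% versus 9% and a null of no difference, the planned test has about 91% power at 640 per arm. That conclusion depends on reading the 6% as the expected absolute effect. The article also calls it a limit of superiority, and 640 does not follow from the stated inputs under either sidedness, so the origin of the 80% cannot be checked. Changing the sidedness alone would leave that gap.

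**What to change.** In Sample Size Calculation:

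1. Replace the 1-sided α of .05 with 2-sided α = .05 (equivalently 1-sided .025), to match the two analysis sections.
2. State the expected effect and any superiority margin as separate quantities, and say which of them the 6% is.
3. Restate the power of 640 per arm for the planned test: about 91% for 15% versus 9% against a null of no difference. If a margin was used to reach 640, disclose it, give the power on that basis, and make clear whether the primary test is meant to use it.

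The cost is a rewritten sample size paragraph. No patients are added. If a margin turns out to have been used, the sponsor must accept a less favourable stated power for the margin-based test (about 70% under the assumed 1.5 points).

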### Prespecified Substudies

The primary purpose of this study is to determine whether tropisetron can lower the risk of emergence delirium and other delirium or treatment related outcomes. In addition, we will collect data on changes of blood biomarkers, EEG behaviors, and clinically relevant outcomes. Substudies derived from this trial are encouraged, with aim of providing more evidence on the following clinically relevant outcomes:

EEG behaviors and postoperative delirium. The role of EEG patterns for estimating and detecting delirium remains inconclusive.^44,45,46^ The present study will allow for this investigation, because EEG data are collected at baseline, the intraoperative period, and the postoperative period. We will explore the association between EEG behaviors and postoperative outcomes (eg, emergence delirium and postoperative delirium).Association between blood biomarkers and postoperative delirium. Previous studies^47,48^ have evaluated the molecular levels of biomarkers associated with detection and/or estimating outcomes of postoperative delirium. In the present study, preoperative and postoperative blood samples were evaluated to explore for the association of potential biomarkers with the risk of postoperative delirium.Effect of preoperative psychiatric and cognitive status on postoperative delirium. The cognitive status has an impact on development of postoperative delirium.^49,50^ We will explore the association between preoperative psychiatric and cognitive status (eg, anxiety, depression, insomnia, and cognitive impairment) and postoperative delirium.Perioperative depressive symptoms outcomes. Depressive symptoms are a common and important complication of major surgery and associated with worse quality of life and even morality.^51^ Depressive symptoms at postoperative day 3 will be assessed and mechanisms will be explored, including risk factors, pain, and general health status.Anxiety symptoms outcomes. The occurrence of anxiety has been shown to be associated with high levels of pain, prolonged hospital stays, and long-term dissatisfaction.^52^ Preoperative and postoperative anxiety symptoms will be assessed to determine clinical factors associated with presenting anxiety symptoms and postoperative outcomes (pain and general health status) associated with anxiety.Association between insomnia and postoperative outcomes. Insomnia has previously been associated with clinically relevant outcomes.^53^ The study will assess the effect of preoperative insomnia on postoperative outcomes (pain and general health status).

